### Randomisation

Participants will be randomised with a 1:1 treatment allocation to the intervention group or usual care group 2 weeks after TKR. Prior to randomisation, eligibility criteria will be reassessed through contact with participants and review of operation notes. Randomisation with allocation concealment will be conducted by means of a computer-generated code, administered centrally and communicated via the Internet (through the Bristol Clinical Trials and Evaluation Unit). Randomisation will be stratified by pre-operative function measured by the Lower Extremity Functional Scale [27] (categorised as high or low function based on mean scores from a published study with a similar patient cohort [28]) and recruitment centre (Southmead Hospital or Emersons Green Treatment Centre). Blinding of participants and trial personnel to treatment allocation will not be possible due to the nature of the intervention.

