### Sample size

The minimal clinically important difference (MCID) for the LEFS is 9 scale points [26]. In our feasibility study, we observed a pooled standard deviation (SD) of 18.4 and a rate of missing LEFS score of 9 % in the intervention group and 35 % in the usual-care group at 6 months post-operative. For the purposes of the sample size calculation we assumed a similar SD for the LEFS at 12 months post-operative, due to the lack of relevant published data. To account for the uncertainty induced by estimating parameters from a small feasibility study, we adjusted the assessed sample by an inflation factor of 1.12^2^, a value derived from the 80 % upper confidence limit of the SD estimate [46]. We also accounted for a missing data rate of 35 %, although we are implementing additional measures to improve LEFS completion rates (e.g. completion of the primary outcome measure over the telephone with non-responders). Therefore, a sample of 256 patients will allow us to detect a MCID (9 points) in the LEFS between trial arms at 12 months post-operative, assuming a power of 80 %, a two-sided 5 % significance level and accounting for up to 35 % missing data and an ‘inflation factor’ of 1.12^2^.

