### Statistical analysis

Analysis will follow a Statistical and Health Economics Analysis Plan which will have been approved a priori by the Trial Steering Committee. Data presentation and analysis will be in accordance with Consolidated Standards of Reporting Trials (CONSORT) guidelines. Baseline characteristics will be reported by trial arm using percentages, means (SDs) or medians (interquartile ranges) as appropriate. The repeated measures of primary and secondary outcomes will be plotted by trial arm.

The main analysis will consist of a linear mixed regression (with random intercept for patient to control for the repeated follow-ups) with an interaction between the intervention effect and the assessment time adjusted for pre-operative function and recruitment centre. The use of these interactions terms will allow us to assess and single out the specific effect of the intervention on LEFS at 12 months post-operative, and then identify the intervention-specific effects at 3 and 6 months post-operative (secondary outcomes). The regression will then be adjusted for imbalanced individual characteristics between arms at baseline. Other types of generalised linear mixed models will be considered if the former approach is not fitting the distribution of the residuals of the regressed (transformed) primary or secondary outcomes. The model will finally be adjusted for type of additional physiotherapy treatment received (physiotherapy received that is not delivered as part of the intervention). The trial is not powered for such adjustments and it will only inform us on their potential impact on the intervention effect.

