The analyses will be conducted on an intention-to-treat basis with and without imputation of missing primary outcome data. A multiple imputation (MI) by chained equations under a missing at random framework stratified by randomization arm will be used [47]. These imputed results will be contrasted with other imputation strategies as discussed by White and colleagues [48]. The same modelling strategy will be used to investigate the intervention effect on the KOOS, HADS and patient satisfaction. A sensitivity analysis will investigate the intervention effect using a per-protocol analysis. Information clustering at the recruitment centre level will be addressed using a fixed-effect indicator and clustering of outcomes by surgeon will be investigated and modelled if required. We will also compare the mean/median primary outcome by physiotherapist for patients receiving the intervention and any significant differences will be used to conduct exploratory sub-group analyses. Given the differences in outcomes after TKR for men and women [49], exploratory analysis will be undertaken to investigate the impact of gender.

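### KOOS and HADS inherit a model adjusted for pre-operative function and centre, with no pre-specified term for each outcome's own pre-operative score

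*Protocol article*

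**What the plan says.** The protocol article describes the main LEFS analysis as a linear mixed regression with a treatment-by-time interaction, "adjusted for pre-operative function and recruitment centre" (Statistical analysis). A later step adds individual characteristics found to be imbalanced between arms at baseline. The same section then extends the approach: "The same modelling strategy will be used to investigate the intervention effect on the KOOS, HADS and patient satisfaction".

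Three other places bear on this:

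- **Patient characteristics** lists LEFS, KOOS, EQ-5D-5L and HADS as pre-operative measures and gives later adjustment in the analysis as the reason for collecting them.
- **Randomisation** stratifies by centre and by pre-operative LEFS, "categorised as high or low function based on mean scores from a published study with a similar patient cohort". This is the only place where a two-level form of function appears.
- **Health economic analysis** adjusts costs and QALYs for the stratification variables and, for QALYs, separately names baseline utility.

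The article refers to a Statistical and Health Economics Analysis Plan, which is not available here.

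**The concern.** For the LEFS, pre-operative function is the outcome's own baseline, so the named covariate suits the outcome. Carried literally to HADS anxiety, HADS depression and the KOOS domains, it is a different variable. Each of those scales has a pre-operative score that will usually predict its follow-up value better than lower-limb function does.

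The only stated route for those scores into the model is the imbalance step. That makes the covariate set depend on the observed data, and the article gives no criterion for imbalance. It also selects on the wrong property: the gain from adjusting for a baseline score depends on how well it predicts the outcome, and exists whether or not the arms happen to differ on it.

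At stake are wider intervals than the collected data allow for KOOS and HADS, and effect estimates that move with chance baseline differences too small to trigger the imbalance step.

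**Working it through.** **1. The plan's own figure.** Inputs from Sample size: "The minimal clinically important difference (MCID) for the LEFS is 9 scale points"; "we observed a pooled standard deviation (SD) of 18.4"; "we adjusted the assessed sample by an inflation factor of 1.12^2"; "We also accounted for a missing data rate of 35" per cent; "assuming a power of 80 %, a two-sided 5 % significance level".

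- Inflated SD = 18.4 × 1.12 = 20.608.
- n per arm = 2 × [20.608 × (1.960 + 0.842) / 9]² = 82.3, rounded up to 83.
- Allowing for missing data: 83 / 0.65 = 127.7, rounded up to 128 per arm, 256 in total.

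The stated 256 is reproduced. The calculation uses no baseline covariate, so nothing below alters it.

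**2. Which covariates are fixed.** Statistical analysis names function and centre, makes further baseline characteristics conditional on imbalance, and applies the same strategy to KOOS and HADS. No sentence there names an own-baseline term for those outcomes. Health economic analysis does name one, for QALYs.

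**3. Precision for KOOS and HADS.** The documents give no baseline–outcome correlations, so these are assumptions. Let r be an outcome's correlation with its own pre-operative score and c its correlation with pre-operative function. At a single follow-up time, ignoring centre, the residual variance as a fraction of the unadjusted variance is:

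- own continuous baseline: 1 − r²
- continuous function only: 1 − c²
- function as high/low, split at the median of a normal score: 1 − c² × 2/π, with 2/π = 0.637

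Variance without the own baseline divided by variance with it:

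| r | c | continuous function: (1 − c²)/(1 − r²) | high/low function: (1 − 0.637c²)/(1 − r²) |
|---|---|---|---|
| 0.3 | 0.3 | 0.910/0.910 = 1.00 | 0.943/0.910 = 1.04 |
| 0.3 | 0.1 | 0.990/0.910 = 1.09 | 0.994/0.910 = 1.09 |
| 0.4 | 0.2 | 0.960/0.840 = 1.14 | 0.975/0.840 = 1.16 |
| 0.5 | 0.3 | 0.910/0.750 = 1.21 | 0.943/0.750 = 1.26 |
| 0.6 | 0.3 | 0.910/0.640 = 1.42 | 0.943/0.640 = 1.47 |
| 0.6 | 0.1 | 0.990/0.640 = 1.55 | 0.994/0.640 = 1.55 |

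At r = 0.5 and c = 0.3, intervals are wider by √1.21 = 1.10 to √1.26 = 1.12 times. The equivalent loss of patients is 1 − 1/1.21 = 17 % to 1 − 1/1.26 = 21 %.

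**4. The LEFS, if the high/low stratum were the covariate.** The ratio is (1 − 0.637r²)/(1 − r²): 1.04 at r = 0.3, 0.841/0.750 = 1.12 at r = 0.5, and 1.35 at r = 0.7. With 83 analysed per arm and r = 0.5, power would be about 80 % unadjusted, 87 % with high/low and 90 % with the continuous score. A 12 % higher variance equals an effective sample loss of 1 − 1/1.12 = 11 %. These figures are conditional, because the protocol does not state that the model uses the category.

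**The case against.** The strongest reply is that the same strategy need not mean the same covariates. For the LEFS, pre-operative function is the own baseline, so the natural translation is each outcome with its own baseline. The stated reason for collecting pre-operative KOOS and HADS points the same way, and a condensed article may leave the covariate list to its analysis plan. This has force: the text neither names nor excludes an own-baseline term, so a reader who infers that the protocol rejects own-baseline adjustment goes too far. What remains is that the article does name its covariates and does make other baseline variables conditional on imbalance. If unconditional own-baseline adjustment was meant, the imbalance rule conflicts with it.

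A reader might also infer that the LEFS model uses the high/low category and so wastes information in the primary analysis. The documents do not support this. The split is described only as a randomisation stratum. The analysis section speaks of pre-operative function without giving its form, and the economic section uses a different term when it means the stratification variables. The form of a covariate is ordinary analysis-plan detail.

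A third tempting inference is bias. Randomisation keeps the comparison valid without own-baseline adjustment, and the imbalance step would deal with marked chance differences. The Discussion also calls analyses other than the primary exploratory. These points limit the importance of the matter but do not remove the gain from pre-specification.

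**Conclusion.** The point holds as a minor one about precision and pre-specification in secondary outcomes. On the text as written, KOOS and HADS have no planned own-baseline term, although the scores are collected for adjustment. The likely cost ranges from nothing to about 55 % more variance, and is about 20 to 26 % at the middle values.

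That range rests on assumed correlations, a single-time-point approximation and, for the high/low form, a normal score split at its median; a cut away from this cohort's median would lose more. The loss would be smallest where a KOOS domain overlaps with what the LEFS measures, such as function in daily living. It would be larger where the outcome is only weakly related to function, as HADS may be.

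No loss is shown for the LEFS. The sample size, significance level, stated power and primary conclusion are unaffected.

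**What to change.** State in the analysis plan, and in the protocol if it is amended, that each outcome is adjusted for its own continuous pre-operative score plus the stratification factors, whatever imbalance is observed. That means LEFS for LEFS, each KOOS domain for itself, HADS anxiety for HADS anxiety, and HADS depression for HADS depression. Satisfaction has no pre-operative measurement and uses the stratification factors only. Adjustment for other characteristics found to be imbalanced can remain as a separate, supplementary step.

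The same sentence settles the form of the function covariate for the LEFS. The cost is the wording alone: the scores are already in the pre-operative questionnaire, and no extra data, patients or design change are needed. It should be fixed before outcome data are examined by arm. If the analysis plan already says this, nothing further is required.

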**Methods/design:**

Two hundred and fifty-six patients waiting for knee replacement because of osteoarthritis will be recruited from two orthopaedic centres. Participants randomised to the usual-care group (*n* = 128) will be given a booklet about exercise and referred for physiotherapy if deemed appropriate by the clinical care team. The intervention group (*n* = 128) will receive the same usual care and additionally be invited to attend a group-based outpatient physiotherapy class starting 6 weeks after surgery. The 1-hour class will be run on a weekly basis over 6 weeks and will involve task-orientated and individualised exercises.

The primary outcome will be the Lower Extremity Functional Scale at 12 months post-operative. Secondary outcomes include: quality of life, knee pain and function, depression, anxiety and satisfaction. Data collection will be by questionnaire prior to surgery and 3, 6 and 12 months after surgery and will include a resource-use questionnaire to enable a trial-based economic evaluation. Trial participation and satisfaction with the classes will be evaluated through structured telephone interviews. The primary statistical and economic analyses will be conducted on an intention-to-treat basis with and without imputation of missing data. The primary economic result will estimate the incremental cost per quality-adjusted life year gained from this intervention from a National Health Services (NHS) and personal social services perspective.

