### Participant recruitment

NHS patients will be screened and recruited from pre-operative assessment clinics at two elective orthopaedic centres in Bristol: Southmead Hospital and Emersons Green Independent Treatment Centre. Inclusion criteria include NHS patients aged 18 years or older who are listed for primary TKR due to OA. Exclusion criteria include (1) patients listed for TKR for reasons other than OA, (2) patients listed for revision TKR, (3) inability to participate in exercise for medical reasons such as unstable cardiovascular or severe neurological conditions, (4) unable or unwilling to attend physiotherapy classes after surgery, (5) unable or unwilling to provide informed consent, (6) inability to understand English because not all the questionnaires have been translated and validated into other languages, and (7) post-operative complication(s) or interventions within the first 2 weeks of surgery which would preclude participation in the physiotherapy classes; for example, prosthetic joint infection or manipulation under anaesthetic. Participation in pre-operative physiotherapy was not a selection criterion for this trial. In order to explore whether the patients who are enrolled in the trial are representative of those undergoing TKR, anonymised data about age and gender will be recorded for all eligible patients. After patients who wish to participate in the trial have provided written, informed consent, they will be asked to complete a pre-operative questionnaire.

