### Usual care

At both recruitment centres, usual physiotherapy after discharge following TKR surgery comprises information and advice on knee-specific and functional exercise. Referral for outpatient physiotherapy is on a needs-only basis when deemed appropriate by a member of the clinical care team. Prior to hospital discharge, patients are assessed on an individual basis by the inpatient physiotherapy team at each centre, and patients with poor range of motion or muscular weakness are referred for outpatient community-based physiotherapy. This referral is at the discretion of the hospital’s physiotherapy or orthopaedic team. General practitioners (GPs) and consultants can also refer patients for outpatient physiotherapy as appropriate. Use of physiotherapy services by participants in both trial arms will be recorded in the trial questionnaires.

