### Intervention

Participants allocated to the intervention group will receive the intervention in addition to usual care. The intervention is a novel weekly 1-hour physiotherapy class, starting 6 weeks after surgery and then on a weekly basis over 6 consecutive weeks. Previous trials have evaluated outpatient physiotherapy after TKR [20]; however, this intervention is novel as it embeds individualised exercises within a group-based task-oriented exercise circuit. The design of the intervention was informed by intervention development work, which included a systematic review [20], survey of current practice [14] and a feasibility study to pilot the intervention [25]. The intervention consists of task-orientated exercises and individualised exercises. Previous research has demonstrated the benefits of task-orientated, functional exercises [19] and the importance of improving patients’ ability to participate in ‘valued activities’ [8, 29]. Task-orientated exercises have been found to be more effective than traditional exercises, such as range of motion exercises, in improving function and participation after TKR [19] and other conditions such as stroke [30]. The inclusion of individualised exercises aims to address patients’ expectations, empower people to take an active role in rehabilitation, and increase self-efficacy [31, 32]. Delivery is in a group-based setting, which can be a cost-effective way to deliver rehabilitation without compromising effectiveness [33–35]. There is currently no consensus on the optimal treatment frequency or number of sessions for physiotherapy after TKR [36]. The intensity of our intervention was informed by previous research [20], combined with the need to develop an intervention that would be deliverable within the NHS if proven to be effective.

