### Resource use

Resource-use data will be collected from hospital discharge to 12 months post-operative. Resources required to deliver the intervention will be recorded in Case Report Forms by the physiotherapists delivering the intervention. Patient self-report use of services will be collected through patient-completed resource-use questionnaires. The questions will cover the use of additional physiotherapy treatments in hospital and community and other therapies prescribed, readmissions, outpatient visits, GP and nurse visits, medication use and use of social services. To allow for a secondary societal analysis, questionnaires will further collect time off work, leisure activities, private expenditures (e.g. privately paid therapies, travel costs to sessions) and informal care. All participants will be provided with a resource-use log to prospectively fill in resources used to aid them in the completion of the resource-use questionnaires [44].

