## Discussion

This project is a fully powered RCT to evaluate the long-term clinical effectiveness and cost-effectiveness of a novel group-based outpatient physiotherapy intervention following TKR in addition to usual care. The trial includes patients with all levels of functional aspirations, and emphasises the concept of participation in valued activities as a basis for effective and appropriate rehabilitation goals. Our approach aims to both improve function for those patients who may otherwise have unfavourable outcomes, and assist patients who are recovering well to achieve more demanding goals.

A strength of this trial is that the design of the intervention and trial were informed by prior feasibility work [25]. In particular, the feasibility work highlighted the importance of complementing the collection of outcome measures by postal questionnaire with telephone calls to maximise completion rates. This has previously been shown to be an effective strategy with a similar patient population [56], although with the increasing uptake of technology, online questionnaires may be a useful alternative data collection method for future trials. Another strength of this trial is the 12-month follow-up period, which will allow assessment of the long-term impact of physiotherapy on patient outcomes and resource use. However, in addition to patient-reported outcome measures, the trial may have benefitted from the inclusion of more objective measures of function, such as muscle strength or gait analysis, as these capture different dimensions of function [57]. Another limitation of the trial which warrants acknowledgement is the lack of blinding, because of the group-based nature of the physiotherapy intervention. Blinding in trials of physiotherapy is often challenging and only a quarter of physiotherapy trials are blinded [58]. There is a risk that lack of blinding will introduce bias as outcome data will be self-reported by participants who will know which treatment they have been allocated to. A recent meta-epidemiology study found that lack of blinding in physiotherapy trials can lead to an underestimation of the treatment effects compared to trials with blinding, although this was not statistically significant [58]. In addition, while the trial is powered for our primary analysis, other analyses are purely exploratory in nature and will be interpreted as such.

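### The per-protocol analysis is open to selection bias if it rests on class attendance, and does not test the intention-to-treat result; add a complier average causal effect

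*Protocol article*

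**What the plan says.** The main analysis keeps participants as randomised. The Statistical analysis section says: "The analyses will be conducted on an intention-to-treat basis with and without imputation of missing primary outcome data". Later in that section comes the only analysis by class adherence: "A sensitivity analysis will investigate the intervention effect using a per-protocol analysis". The article does not define the per-protocol population. It also defers detail to a Statistical and Health Economics Analysis Plan, which is not shown.

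Four other places bear on the point:

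- **Who has classes to attend.** The Intervention section says: "Participants allocated to the intervention group will receive the intervention in addition to usual care". The Abstract adds that these participants will "additionally be invited to attend a group-based outpatient physiotherapy class starting 6 weeks after surgery". Randomisation is 2 weeks after surgery, so attendance follows allocation.
- **Screening.** Participant recruitment excludes patients who are "unable or unwilling to attend physiotherapy classes after surgery".
- **Other physiotherapy.** Usual care says: "Use of physiotherapy services by participants in both trial arms will be recorded in the trial questionnaires".
- **Status.** The Discussion says that, beyond the primary analysis, "other analyses are purely exploratory in nature and will be interpreted as such".

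**The concern.** A usual-care patient has no classes to miss. A rule based on class attendance can therefore remove people from one arm only. It drops intervention patients who did not attend and keeps the usual-care patients who would not have attended had they been invited. If the two kinds of patient differ in prognosis, the remaining groups are no longer comparable.

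A rule that excluded usual-care patients for receiving other physiotherapy would not restore the balance. The Usual care section says that referral is for restricted knee movement or weak muscles, which is itself prognostic.

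The label also misleads. A sensitivity analysis varies the assumptions behind one estimate. A per-protocol analysis aims at another quantity, so agreement or disagreement with the intention-to-treat result says little about how robust that result is. In a superiority trial it is not a conservative check either. What is at stake is interpretation: after a null primary result, a positive per-protocol result could be taken to show that the classes work for those who attend, when it may only reflect who attends.

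**Working it through.** **1. The plan's own figure.** Inputs from the Sample size section: MCID 9, SD 18.4, two-sided 5%, power 80%, inflation factor 1.12², 35% missing.

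- No inflation: 2 × (1.96 + 0.84)² × 18.4² / 9² gives 66 per arm.
- SD 18.4 × 1.12 = 20.6: 83 per arm.
- 83 / 0.65 = 127.7, so 128 per arm and 256 in total.

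The stated 256 is reproduced. Nothing below challenges it.

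**2. The formulas.** Let *p* be the share of the intervention arm that attends, *g* the mean LEFS of would-be attenders minus that of would-be non-attenders when neither has classes, and *e* the effect in attenders. Assume no effect in non-attenders.

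- Attenders against all usual care: (attender mean + *e*) − [*p* × attender mean + (1 − *p*) × non-attender mean] = *e* + (1 − *p*) × *g*. The bias is (1 − *p*) × *g*.
- Intention to treat: *p* × *e*.
- Complier effect: intention to treat / *p* = *e*.

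**3. The numbers.** The documents give neither *p* nor *g*; both are assumptions. I take *p* from 0.6 to 0.9, and *g* of 0.25 SD (0.25 × 18.4 = 4.6 points) or 0.5 SD (9.2 points). With 83 evaluable per arm, the intention-to-treat standard error is 18.4 × √(2/83) = 2.86, and the complier standard error is about 2.86 / *p*.

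| *p* | Bias, *g* = 4.6 | Bias, *g* = 9.2 | Per-protocol false-positive rate, *g* = 9.2, no effect | Intention to treat if *e* = 9 | Complier SE |
|---|---|---|---|---|---|
| 0.9 | 0.46 | 0.92 | 6% | 8.1 | 3.17 |
| 0.8 | 0.92 | 1.84 | 9% | 7.2 | 3.57 |
| 0.7 | 1.38 | 2.76 | 14% | 6.3 | 4.08 |
| 0.6 | 1.84 | 3.68 | 20% | 5.4 | 4.76 |

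The bias runs from 0.46 / 9 = 5% to 3.68 / 9 = 41% of the MCID. The false-positive column compares with a nominal 5%.

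**4. Direction.** If *g* = 0 the bias is zero. If attenders have the worse prognosis the sign turns: with *g* = −4.6 the bias is −0.46 to −1.84.

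**5. Simulation** (4,000 trials per scenario, 83 per arm, SD 18.4, *g* = 9.2; *p* = 0.9, 0.8, 0.7).

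- No true effect: the per-protocol mean was 0.90, 1.85 and 2.80; intention to treat / *p* averaged −0.04, −0.03 and −0.02.
- Complier effect of 9: per-protocol gave 9.88, 10.81 and 11.79; intention to treat / *p* gave 8.94, 8.94 and 9.01.

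These are unadjusted comparisons of 12-month means. In an adjusted model, *g* is the gap that remains after the baseline covariates.

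**The case against.** The strongest reply is that the article commits to very little. A reader might infer that it plans to compare self-selected attenders with all usual-care patients in order to estimate the effect of taking the classes. It says neither. The population definition may stand in the unseen analysis plan, and exclusions could be made in both arms because other physiotherapy is recorded in both. This stands as to what the article states. It does not rescue the method: a rule based on attendance works on one arm only, and a rule based on other physiotherapy removes patients selected by prognosis.

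A reader might also infer that the analysis is certainly biased in favour of the intervention. The documents do not support that. Patients who recover well may skip classes, which would reverse the bias. Several features should limit non-attendance: the exclusion of those unwilling to attend, the recheck of eligibility before randomisation, and travel reimbursement. At 90% attendance and a gap of 0.25 SD the bias is under half a point.

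Nor is the complier estimate unbiased, as a reader might conclude. Two-stage least squares is consistent, and only if allocation acts solely through attendance. That is debatable here: outcomes are self-reported without blinding, and participants set activity goals before their first class. A threshold that counts partial attendance as none also strains the condition, and using the number of sessions assumes an equal effect per session. Missing outcomes (9% against 35% in the feasibility study) threaten both methods.

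Finally, the Discussion calls all but the primary analysis exploratory. That lowers the stakes, but it does not correct a biased estimate.

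**Conclusion.** The concern holds in limited form. The one named analysis by adherence is likely to depend on a choice made after randomisation and available in one arm only. It is therefore open to selection bias and is misdescribed as a sensitivity analysis of the intention-to-treat effect. Under the assumed 60-90% attendance and a 0.25-0.5 SD advantage for attenders, the bias is about 0.5-3.7 LEFS points; its true size and sign are unknown. Because the classes are meant for one arm only, the design suits an estimate that keeps the randomised comparison, and the article names none. The consequence is confined to a secondary, exploratory result.

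**What to change.** Add to the analysis plan, as a supplementary estimand, a complier average causal effect for LEFS at 12 months. Estimate it by two-stage least squares with randomised arm as the instrument for class attendance, adjusting for the primary model's baseline covariates (pre-operative function and recruitment centre). Because the trial is open, fix the definition of attendance before outcome data are analysed. Drop the per-protocol analysis or label it descriptive.

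State that the estimate is consistent, not unbiased, and only if:

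- usual-care patients cannot access the classes;
- allocation affects the outcome only through attendance;
- missing outcomes are handled validly.

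Confirm that attendance is captured for each participant. The Resource use section says "Resources required to deliver the intervention will be recorded in Case Report Forms by the physiotherapists delivering the intervention", but does not name individual attendance as an item.

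The cost is plan wording, one extra model, an exclusion restriction that cannot be tested, and a wider interval: a standard error of 3.17-4.76 against 2.86 for intention to treat, under the assumptions above. No extra patients are needed.
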